## Methods/design

### Study design

In this protocol, we describe a four-armed randomized controlled trial with measurement bursts (i.e., periods of intensive longitudinal data collection) conducted to compare the efficacy of two 6-week online interventions for recovery from work. We will randomly assign the participants to one of four conditions: (a) experimental condition 1: CBT-based techniques, (b) experimental condition 2: mindfulness-based techniques, (c) waitlist condition 1: CBT-based techniques, (d) waitlist condition 2: mindfulness-based techniques. To monitor progress for the assessments, we will maintain a parallel structure for all four groups, meaning that the waitlist control groups will respond to the same questionnaires in all phases of the study. We will invite all participants via email to complete the pretest (Phase 1) and the first measurement burst (comprising four daily assessments from Monday through Friday plus one assessment on Saturday morning). This first week of intensive assessments represents Phase 2. After Phase 2, participants in the experimental groups will immediately receive access to the online interventions. During the 6 weeks of the interventions in both experimental groups, participants in all groups will be prompted once a week to provide 1 day of experience-sampling measures (four daily assessments, Phase 3). Approximately 7 weeks after Phase 2, participants will begin the second week of intensive longitudinal assessments (similar to Phase 2) followed by the posttest (Phase 4). Following Phase 4, individuals in the waitlist control groups will receive access to the online training programs in either the CBT-based or mindfulness-based form—depending on their allocation at the start of the study. Finally, Phase 5 will take place 3 months after the end of Phase 4 and will again include 1 week of intensive longitudinal assessments and a follow-up assessment (similar to Phase 4).

### Participants and recruitment

The study will be conducted with employed volunteers recruited through newspapers, flyers, and social media. To estimate the power to detect an assumed meta-analytical pre-post effect of *d* = 0.36 [42], if such an effect exists in the population, we ran a Monte Carlo simulation. Our analyses for the primary outcome involve a Latent Change Model (see below for more details). The simulations showed that for a two-tailed test with 90% power and a priori alpha level of 5%, we would need *N* = 136 participants in each experimental group to be able to detect a pre-post difference of approximately *d* = 0.35 (in our case represented by the intercept of the latent change factor) if it exists in the population.

In addition, for the analyses of the dynamic associations with the measurement bursts, previous studies have shown that the power to detect a relatively small standardized indirect effect of 0.1 was = 0.81 for ICC ≥ 0.10 with *J* ≥ 100 clusters with a within-cluster sample size of *n *_*j*_ = 20 [56]. Because our research questions refer in part to the upper levels of the hierarchical data, we will need a sample size that will allow us to estimate unbiased parameters for the mediation models at the person-level of analysis as well. Li and Beretvas [57] showed that a multilevel SEM required at least 80 clusters to circumvent convergence issues.

Considering all the analyses' requirements and assuming a drop-out rate of up to 20% after Phase 3 and up to an additional 20% after Phase 4, we aim to recruit 600 participants (i.e., 480 in Phase 4 and 384 in Phase 5). The analyses will be conducted using all available data (either with Full Information Maximum Likelihood or Bayesian estimation). To be eligible for this study, participants must (1) be 18 years or older, (2) be working regular working hours (no shift work) at least part-time, (3) not be in psychotherapeutic or psychiatric treatment, and (4) be smartphone users with mobile internet access. In addition, participants must be able to read and write in German.

Individuals interested in participating will be able to register on the project's website, freiraum-im-kopf.de. The website contains information about the study's aims, procedure, assessments, data protection policy, and informed consent. The informed consent form explains that individual data will remain confidential. That is, all records that contain names or other personal identifiers, will be stored separately from study records identified by code number. We inform that data will be published in an anonymized form in a repository parallel to the publication. Also, participants will be assured that they may withdraw from the study at any time. A researcher not involved in the study will randomly allocate participants to one of four study conditions (see Fig. 1) using computer-generated random numbers. We plan to oversample the experimental conditions to include two thirds of all participants using block randomization. This procedure ensures an equal random distribution of the individuals into all four groups. We will ensure allocation concealment, as the randomization code will not be available to the trial investigators until the participants have completed all baseline measurements.

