**Methods:**

In this randomized, waitlist controlled trial, we will investigate the effectiveness of two 6-week online training programs (cognitive behavioral and mindfulness-based). The sample will include employees working at least part-time during regular work hours. Besides the pre-post-follow-up assessments, the trial will include measurement bursts with the goal of examining the underlying mechanisms. We expect that both interventions will reduce work-related perseverative thinking (PT) compared with the waitlist control groups (primary outcome). Also, we expect that both interventions will result in similar improvements, but the underlying mechanisms will differ (process outcomes). In the cognitive-behavioral intervention group, we expect that the main mechanism responsible for lower PT levels will be an increase in recovery experiences across time. In the mindfulness-based group, we expect that the main mechanism responsible for lower PT levels will be an increase in facets of mindfulness across time.

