### Interventions promoting recovery and reducing work-related perseverative thinking

In 2011, Cropley and Zijlstra raised the concern that "there is a distinct lack of studies that have put forward interventions to help people to switch-off, unwind and recover post work" [36] (p. 495). Similarly, Ebert and colleagues (2015) stated that given that interventions for individuals with work-related mental health problems are more effective when work-related aspects are considered, "the limited amount of intervention research on combined interventions that target recovery by improving effective psychological detachment from work and sleep is surprising" [37] (p. 1241).

Meanwhile, various approaches have been designed and evaluated. Several interventions have successfully addressed detachment or repetitive work-related thinking directly [37, 38]. Others have focused on other constructs, such as improving boundary management [39], stress management skills [40], or mindfulness [41]. Hence, in this second group of interventions, increasing detachment or reducing PT was not the primary goal, but these interventions fostered detachment nevertheless.

A recent meta-analysis of interventions that were aimed at fostering detachment [42] stated that, on average, the existing heterogeneous intervention approaches yielded a positive small to moderate effect (*d* = 0.36) on detachment. Interventions that included multiple strategies, such as engagement in recovery activities, boundary management, mindfulness, and more general emotion regulation techniques, were the most successful. In addition, interventions lasting more than 2 weeks and with a higher dosage (in total more than 4 h) were more successful than briefer and lower dosage trainings.

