## Research goals

The first goal of this randomized controlled trial is to compare the efficacy of two online training programs promoting recovery from work. We hypothesize that participants in the two experimental conditions (CBT-based and mindfulness-based training) will experience lower levels of work-related PT (primary outcome) after the intervention. No prediction can be made from previous literature as to which of the two interventions would be more effective. Therefore, we assume that the two experimental conditions will not differ with regard to their effectiveness in reducing the primary outcome.

The second goal of the present study is to explore the mechanisms related to recovery from work and its improvement on a daily level. Hence, using the data from the experience sampling phases of the study, we will investigate within- and between-day variables and processes that may account for the overall effect of the intervention—and, in addition, may further qualify the expected effect.

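### The stated 90% power is for a within-group pre-post change and does not carry over to the comparison with the waitlist that the primary hypothesis names

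*Protocol article*

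**What the plan says.** Participants and recruitment sets out the power calculation. It begins "To estimate the power to detect an assumed meta-analytical pre-post effect of" d = 0.36, taken from a meta-analysis. The Monte Carlo simulation is described as being "for a two-tailed test with 90% power and a priori alpha level of 5" per cent. It returns N = 136 "participants in each experimental group to be able to detect a pre-post difference of approximately" d = 0.35, with the tested quantity "in our case represented by the intercept of the latent change factor". The target is 600 recruited, 480 at Phase 4 and 384 at Phase 5.

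The Methods part of the Abstract states the primary hypothesis: "We expect that both interventions will reduce work-related perseverative thinking (PT) compared with the waitlist control groups (primary outcome"). Research goals repeats it without a comparator: participants in the two programs "will experience lower levels of work-related PT (primary outcome) after the intervention".

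Data analyses estimates the latent variables separately in three groups: each experimental group, and the two waitlist groups combined. It places an N(0, 0.010) prior on the difference in pre-post change between the two programs.

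On the source of the planning effect, the Background says of the meta-analysis of detachment interventions that "on average, the existing heterogeneous intervention approaches yielded a positive small to moderate effect" (d = 0.36), and names detachment as the outcome.

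**The concern.** With the groups estimated separately, the intercept of the latent change factor is the average change in one group. A test that it differs from zero uses no waitlist data. Regression to the mean, seasonal workload or repeated questioning could move it without any effect of the program. The randomized question is whether change in a program exceeds change on the waitlist. The power text includes no waitlist size, waitlist change or between-group difference.

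The power sentence is what a reader would use to judge a null result against the waitlist. If the 90% is carried over to that comparison, a null result may be read more firmly than the stated calculation supports.

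**Working it through.** **Inputs from the article.** Two-sided 5%, 90% power, d = 0.35, N = 136 per experimental group; 600 recruited with up to 20% lost by Phase 4; two thirds allocated to the experimental conditions; waitlist groups pooled for analysis.

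**Inputs not given.** The pre-post correlation r, the loadings and the reliabilities. I take r from 0.2 to 0.7 as an assumption, with variance of change 2(1 − r) in units of the squared baseline SD. All figures use the normal approximation, with (1.960 + 1.2816)² = 10.507.

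**1. Can 136 be reproduced?** For a one-group test, n = 10.507 × V / 0.35², where V is the variance of change.
- V = 1.0 (r = 0.5): 10.507 / 0.1225 = 85.8, so 86.
- V = 1.6 (r = 0.2): 137.2, so 138, close to 136.
- Solving for V at n = 136: 136 × 0.1225 / 10.507 = 1.586, or r = 1 − 1.586/2 = 0.21.

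A two-group contrast of change with V = 0.8 (r = 0.6) also gives 2 × 10.507 × 0.8 / 0.1225 = 137.2, so 138. The stated figure can therefore be neither confirmed nor refuted, and V = 1.586 is an inference from reading 136 as a one-group N.

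**2. Within-group test against between-group contrast.** A mean change has variance V/n. A difference of two mean changes in equal groups has variance 2V/n. At equal d and V, the contrast needs exactly twice the N per group. At V = 1.586 that is 272 per group for 90%. At V = 1.0 it is 171.6, so 172.

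**3. Expected Phase 4 sizes.** Each program: 600 × 2/3 ÷ 2 × 0.8 = 160. Pooled waitlist: 600 × 1/3 × 0.8 = 160.

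**4. Power for one program against the pooled waitlist at 160 per group,** with 0.35 as the net difference. Unadjusted: power = Φ(0.35 / √(2V/160) − 1.960), V = 2(1 − r). Baseline-adjusted: the same with V replaced by 1 − r².

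| r | Unadjusted | Baseline-adjusted |
|---|---|---|
| 0.2 | Φ(2.475 − 1.960) = 70% | Φ(3.195 − 1.960) = 89% |
| 0.5 | Φ(3.130 − 1.960) = 88% | Φ(3.615 − 1.960) = 95% |
| 0.7 | Φ(4.041 − 1.960) = 98% | Φ(4.384 − 1.960) = 99% |

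The unadjusted contrast reaches 90% when 1 − r = 160 × 0.1225 / (4 × 10.507) = 0.466, that is at r of about 0.53.

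**5. Both programs, and the planned prior.** The two contrasts share the waitlist, so their test statistics correlate at 0.5. I simulated 160/160/160 with equal true effects of 0.35, without and with the N(0, 0.010) prior on the between-program difference, treating 0.35 and the prior as being on the same standardized scale. An effect counts as shown when the 95% interval excludes zero.

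| V | One program, no prior | Both, no prior | One program, prior | Both, prior |
|---|---|---|---|---|
| 1.586 | 70% | 56% | about 78% | about 74% |
| 1.0 | 88% | 80% | about 93% | about 90% |

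**The case against.** The strongest objection is that no low power has been shown. The 1.586 comes from applying a one-sample formula to an unseen simulation of a latent-variable model, and 136 fits a two-group contrast at r of about 0.6 equally well. The planned prior pulls the two programs together and sharpens each one's contrast with the waitlist. The article also reports d = 0.45, from the same meta-analysis, for formats other than face-to-face, including web-based ones. At V = 1.586 and 160 per group, 0.45 gives Φ(3.196 − 1.960) = 89% even without the prior. All of this stands. A reader might infer that the trial has far less than 90% power against the waitlist, but the documents do not support that: 70% and 56% are the unfavourable end of a range that extends to 98% or more.

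The power text is also openly labelled as pre-post, and Research goals names no comparator. That is a fair point about candour, but it does not remove the comparator that the Abstract gives for the primary outcome. If the simulation did target a two-group contrast, then its description is wrong and still needs correcting.

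A reader might also treat the use of a detachment effect as an error, since detachment is a secondary outcome here and the article calls its correlation with perseverative thinking moderate. The Background says openly that 0.36 is for detachment, and a moderate correlation does not show that the effect on perseverative thinking is smaller. It is a labelling point.

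Finally, improvement on the waitlist reduces power only if 0.35 is read as gross change within a program. Taken as the net difference, as above, it does not.

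**Conclusion.** The point holds in a limited form. As described, the 90% at N = 136 belongs to one group's mean latent change. The primary hypothesis concerns a difference in change from the waitlist, which needs twice the N per group at the same d and variance. The stated power therefore does not carry over, and the article gives none for that contrast.

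The documents do not show that the trial is underpowered. The result depends on the unstated correlation and reliabilities, on baseline adjustment and on the prior. At the planned Phase 4 sizes, one program against the waitlist has between about 70% and 98% power unadjusted for r from 0.2 to 0.7, and between about 89% and 99% adjusted for baseline. These figures assume 0.35 as the net difference, equal groups of 160, a common variance of change and no measurement error. There is no error in the recruitment arithmetic: 600 × 0.8 = 480 and 480 × 0.8 = 384.

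**What to change.** Rerun the Monte Carlo simulation with the target parameter set to each experimental arm's mean latent pre-post change minus that of the pooled waitlist. Use 160/160/160 and the planned model, including the N(0, 0.010) prior. State the assumed reliabilities, and report power for one program and for both over a stated range of pre-post correlations, for example 0.2 to 0.7. Replace the present power sentence with this result, and add that 0.36 is a detachment effect taken as the net difference in perseverative thinking.

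The cost is one rerun of an existing simulation and a rewritten sentence; the headline figure may be less favourable. Enrolment, allocation and design need not change.

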**Fig. 1 Fig1:**
[figure not shown]
Study design

Considering the high participant burden, to keep participants involved in the study, we will use a bonus system to reward participation. Participants will receive €10 for completing the posttest and another €10 for the follow-up. In Phases 4 and 5, they will receive 50 cents for completing all measures at each (intensive longitudinal) measurement occasion. In addition, to motivate participants to complete as many measures as possible, participants can enter a lottery. The prizes include 10 vouchers worth €20, 20 vouchers worth €40, and 20 vouchers worth €50.

### Procedure

The overall procedure is shown in Fig. 1. The study will combine a longitudinal design with three experience-sampling phases (measurement bursts). After completing the pretest (Phase 1), participants will begin the first 5 days of the experience sampling (Phase 2). In this week, we will assess all work-related and personal variables in daily life (for an overview of all variables, see section on assessments below). During the experience-sampling phases, participants will be prompted once each morning, once in the (late) afternoon, once during the evening, and once directly before going to sleep. The morning and afternoon sessions will take approximately 2 min, whereas the evening and night sessions will take about 5 min each.

Following Phase 2, participants in the intervention groups will begin with either the CBT-based training or the mindfulness-based training. Because both interventions will last for 6 weeks, we will implement the contents of the interventions in both groups sequentially. Both training programs can be considered low-dose interventions [42]. Based on the literature, we do not expect training-related harms or adverse events. However, the study will monitor such adverse effects, and the participants may contact the research team via email at any time during the study.

### Interventions

#### CBT-based training

Overall, the elements of the CBT-based training program are built on the mechanisms suggested in the DRAMMA-model [24]. The model emphasizes the roles that detachment, relaxation, autonomy, mastery, meaning, and affiliation play in determining well-being. Training will begin with psychoeducative kick-off lessons. Here, we will focus on goal attainment, explain rituals for the transition from work to non-work time, and make suggestions about how to find spare time for relaxing activities. Participants will continue by reflecting on their situation in terms of stressors and values (e.g., meaning or affiliation). We will prompt participants to rediscover and reevaluate their values. Furthermore, we will include behavior-change techniques that directly address PT and sleep problems.

#### Mindfulness-based training

The mindfulness-based training program is built on the concepts and techniques of mindfulness-based interventions [58]. Ideas taken from approaches such as mindfulness-based stress reduction [59] may help employees set cognitive-emotional boundaries and disengage from work. Mindfulness practice may raise awareness of work-related thoughts and improve individuals' abilities to come back to the present (non-work) moment. Accordingly, training will begin with psychoeducative elements on shifting attention toward—and remaining anchored in—the present moment. It will further elaborate on the differences between “doing” and “being” modes of mind and formal and informal mindfulness practices. Formal mindfulness practice is fostered by following along with guided exercises and meditations. Alongside the formal meditations, the training program will offer recommendations for implementing informal practices in daily life and actively breaking maladaptive routines. Participants will learn to increase their self-compassion and to explore negative and positive feelings with curiosity. They will then practice noticing but not ruminating about work-related issues. Instead, they will explore how to distance themselves from feelings and thoughts, such as worries about future-related work issues.

### Intervention content, key features, and core themes

The CBT-based and mindfulness-based interventions have different contents. However, with the same goal of facilitating recovery, the two approaches have several parallel key components. The parallel features are related to the delivery of the intervention (e.g., audio recordings and quizzes) and the type of content that has demonstrated high efficacy in recovery interventions. Specifically, both of our interventions include techniques for boundary management, engagement in recovery activities, sleep improvement, and emotion regulation strategies.

#### Psychoeducation

Both interventions include psychoeducative elements. We will invite participants to explore the determinants of stress and well-being from a cognitive-behavioral or mindfulness-focused perspective. Consequently, at least one third of each week’s module will be dedicated to psychoeducation, increasing participants' knowledge on the topic.

#### Audio-guided exercises

The majority of the modules will involve listening to audio instructions ranging from meditations to podcasts, where the speakers discuss specific psychoeducational topics or give examples from everyday life. The scripts for the audio content are designed to form a bond between intervention and participant by addressing the listener directly on several occasions. Relying on audio in addition to written instructions will further allow participants to focus on topics dynamically because they will be able to change modalities according to their preferences, available time, or environment on a particular day.

#### Active and reflective elements

In both interventions, we will ask participants to engage in certain activities, such as setting their relaxation goals for the next week or completing a short quiz. Thereby, participants will be able to reflect on their progress and revisit their answers in an earlier training period as they proceed through the program. Revisiting their own responses and ratings may enhance commitment and promote self-monitoring and self-reflection.

#### Implementing micro-interventions

Beyond the CBT-based and mindfulness-based strategies provided in the interventions, the training sessions will focus on fostering thoughtful and mindful practices in daily life. In each module, participants will be given suggestions for implementing short interventions in their everyday lives. These micro-interventions will include, for example, eating mindfully or generating implementation intentions for pursuing daily recovery goals.

